## Abstract

**Background:**

Posttraumatic stress disorder (PTSD) may develop after exposure to a traumatic event. Eye Movement Desensitization and Reprocessing (EMDR) is an evidence-based psychological treatment for PTSD. It is yet unclear whether eye movements also reduce stress reactivity in PTSD patients. This study aims to test whether eye movements, as provided during Eye Movement Desensitization (EMD), are more effective in reducing stress reactivity in PTSD patients as compared to a retrieval-only control condition.

**Methods:**

The study includes participants who meet criteria of PTSD of the public psychological services in Jakarta and Bandung, Indonesia. One hundred and ten participants are randomly assigned to either an (1) Eye Movement Desensitization group (*n* = 55) or (2) retrieval-only control group (*n* = 55). Participants are assessed at baseline (T0), post-treatment (T1), 1 month (T2), and at 3 months follow-up (T3). Participants are exposed to a script-driven imagery procedure at T0 and T1. The primary outcome is heart rate variability (HRV) stress reactivity during script-driven imagery. Secondary outcomes include heart rate (HR), pre-ejection period (PEP), saliva cortisol levels, PTSD symptoms, neurocognitive functioning, symptoms of anxiety and depression, perceived stress level, and quality of life.

**Discussion:**

If the EMD intervention is effective in reducing stress reactivity outcomes, this would give us more insight into the underlying mechanisms of EMDR’s effectiveness in PTSD symptom reduction.

**Trial registration:**

ISRCTN registry ISRCTN55239132. Registered on 19 December 2017.

**Supplementary Information:**

The online version contains supplementary material available at 10.1186/s13063-021-05100-3.

## Background

In Indonesia, people are at high risk for trauma exposure, including natural disasters, violent crime, sexual harassment, or experiencing a severe accident, which may lead to posttraumatic stress disorder [1, 2]. Therefore, it can be expected that a high prevalence of PTSD may occur in Indonesia. Research on PTSD in Indonesia is limited. According to existing studies, the prevalence rate of PTSD was 47% among adolescents, 6 months following an earthquake in Aceh [3]. Another study by Down et al. found that overall PTSD rate after major natural disasters in Sumatera and Java was 20.9% [4].

Several psychological interventions are applied to deal with PTSD symptoms. The strongest empirical evidence exists for trauma-focused Cognitive Behavioral Therapy (TF-CBT) and Eye Movement Desensitization and Reprocessing (EMDR) [5, 6]. In this study, we focus on EMDR, more specifically, on the first part of this treatment: Eye Movement Desensitization (EMD). Some preliminary evidence exists for the effect of EMDR on stress measures [7, 8]. It is of interest to study how EMD can get under the skin of patients and alter the level of stress reactivity in PTSD patients.

The effect of eye movements in EMDR therapy process has been explained through the working memory theory, which states that both recalling an emotional memory and making eye movements simultaneously, requires working memory capacity. Performing this dual-task requires working memory capacity and renders the memory less vivid and less emotional [9]. Support for this theory has been found in several experimental studies in healthy samples that reported lower vividness and emotionality of negative autobiographic memories after recall with eye movements (e.g., [10, 11]). Although these studies have shown that EMs significantly reduce memory vividness and emotionality of aversive memories, some limitations remain. The majority of these studies were done in non-clinical healthy student samples. Therefore, the results are difficult to translate to clinical PTSD populations (e.g., [12, 13]).

In addition, only a few studies examined whether EMDR improves stress reactivity related to traumatic memory retrieval as part of the arousal and activity cluster of symptoms in PTSD [14]. Stress reactivity is defined as the reactivity of the autonomic nervous system, which is represented by decreased heart rate variability (HRV) and decreased pre-ejection period (PEP), and increased heart rate (HR) in response to a trauma-related stressor [15]. It has been suggested that EMs in EMDR are beneficial and have a distinct effect on psychophysiological responding [16]. The orienting response theory of EMDR states that EMs, or other dual-attention stimuli, elicit an orienting response with associated physiological de-arousal that enhances trauma material processing [17]. The previous studies in non-clinical and clinical participants have found that EMDR led to significant reductions in heart rate and skin conductance responses to trauma recall compared to a relaxed state [16, 18].

Therefore, it is important to examine whether EMD is associated with reduced stress reactivity among clinical PTSD patients. Psychophysiological stress mechanisms that may play a role in PTSD treatment effects include reduced physiological stress reactivity, assessed with heart rate (HR) and heart rate variability (HRV) responses, and neuroendocrine stress response, as indexed by cortisol levels in saliva [19, 20]. HRV represents the change in the time interval between successive heartbeats. HRV provides an index of the parasympathetic nervous system and has been associated with emotional self-regulation [21].

Besides activating autonomic functioning, stress also activates the hypothalamic-pituitary adrenal (HPA) axis. Activation of the HPA axis is indexed by heightened cortisol levels. High levels of saliva cortisol have been associated with general life stress and emotional regulation that influences cognitive function [22, 23].

A previous study has found a significant relationship between PTSD symptoms and neurocognitive deficits, suggesting that PTSD symptoms may also interfere with executive function and may cause impairments in cognitive flexibility [24]. Another study showed that improved neurocognitive functioning might be a potential mechanism for long-term maintenance of treatment gains following CBT for PTSD [25]. This study will focus on specific elements of neurocognitive functioning, including memory, attention, and information processing, and examine whether these indices improve after EMD.

If we find evidence for reduced stress reactivity and improved neurocognitive functioning after EMD, it can help in understanding part of the underlying mechanisms through which EMD exerts its effects on PTSD symptom reduction. To examine this, we will compare EMD with a control condition, consisting of the same procedure as EMD, but without the EM. Furthermore, we will investigate whether PTSD symptom reduction is related to reduced stress reactivity and neurocognitive functioning. We hypothesize that participants with PTSD receiving the EMD condition will show larger stress reactivity reductions in response to trauma scripts and greater improvements in neurocognitive functioning than the retrieval-only control group.

## Objective

This study aims to test whether particularly Eye Movement Desensitization (EMD), the first part of EMDR treatment, is more effective in reducing stress reactivity in PTSD patients, as compared to a retrieval-only control condition. The current study also investigates whether EMD is related to improved neurocognitive function, including memory, attention, and information processing.

## Methods

### Design

Figure 1 shows the randomized clinical trial (RCT) design of this study (see Fig. 1, flow chart of the trial protocol). Assessments during this study will be conducted during baseline (T0), 1-week post-treatment (T1), 1-month follow-up (T2), and 3 months after treatment (T3). The study has been approved by the research Ethics Committee Universitas Padjadjaran Bandung on 2 July 2018. Document number: 3 35/UN6.KEP/EC/2018.

**Fig. 1 Fig1:**
[figure not shown]
Flow chart of the trial protocol

### Inclusion and exclusion criteria

Participants will be included when they meet the following criteria: (1) Diagnostic and Statistical Manual of Mental Disorders, fifth edition (DSM-5) diagnosis of PTSD as diagnosed with the Structured Clinical Interview for DSM-5 disorders (SCID-5) and (2) age of 18 years or older. Participants will be excluded if they meet any of the following criteria (as indicated by SCID-5): (1) current or previous psychotic disorder, (2) current substance use disorder, (3) acute suicidality, and (4) current organic disorder, i.e., epileptic and brain damage.

### Recruitment

Recruitment of participants will take place from 21 April 2019 to 31 December 2020. Participants (*N* = 92) will be recruited at the public psychological services of Jakarta, Bandung, and Cimahi. These public centers are (1) the “Pulih” clinic in Jakarta, (2) the “psychology service Unisba” in Bandung, and (3) the “crisis center Unjani” in Cimahi. Recruitment will be performed by public announcements through brochures, social media (Facebook, a WhatsApp group, and Instagram), and on the website of the Unjani and “Pulih” clinics. Potential participants who are interested in the project can contact the research team by phone. Then, the research team will perform a first eligibility check by phone.”

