#### Sample size

We expect that HRV will decrease in both groups at T1 compared with T0, with a smaller decrease in the EMD group, resulting in greater HRV at T1 in the EMD group compared with the EMD retrieval-only control group. No studies have been carried out yet comparing the effect of EMD to retrieval only on HRV in PTSD patients to inform power calculations. However, based on the theoretical assumptions and studies with other related outcome measures [63, 64], we expect to detect a difference between the EMD condition and retrieval only on HRV of a medium effect size (Cohen’s *d* = 0.4). Power calculations were conducted using G*power software and were based on based on a general linear model (GLM). Linear mixed-effect model can be conceptualized as GLM (repeated measure ANOVA) as a balanced design within independent sampling units, and an unstructured covariance model is assumed [65]. We transformed for Cohen’s *d* = 0.4 into *f* = 0.2. For a 2 between (treatment EMD conditions) X 2 within (baseline, post-treatment) repeated measure ANOVA (*α* = 0.05, power = 0.9, correlation between measures = 0.4, and medium effect-size *f* = 0.2) [7, 66]. A power calculation suggested that a total sample size of *N* = 82 will be required, which is 41 per condition. All power computations were conducted in the G*Power software. Considering drop out of participants, we will recruit an additional 25% extra participants, yielding a total number of 55 participants per condition, thus 110 participants in total.

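### The Recruitment section sets 92 participants while the Abstract and Sample size section set 110; 92 recruits with 25% loss leave 69 completers against the 82 required

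*Protocol article*

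**What the plan says.** Three places in the protocol article give the size of the trial, and they do not agree.

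- **Recruitment:** "Participants (*N* = 92) will be recruited at the public psychological services of Jakarta, Bandung, and Cimahi".
- **Sample size:** "A power calculation suggested that a total sample size of *N* = 82 will be required, which is 41 per condition". The allowance for attrition follows: "Considering drop out of participants, we will recruit an additional 25% extra participants". The inflated figure is then put in these terms: "yielding a total number of 55 participants per condition, thus 110 participants in total".
- **Abstract, Methods:** "One hundred and ten participants are randomly assigned", 55 to each group.

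The Recruitment and Trial status sections also give a closing date for recruitment, 31 December 2020. Neither says how that date relates to a target number.

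**The concern.** The Recruitment and Sample size sections both speak of participants to be recruited, yet their totals differ by 110 − 92 = 18. Nothing marks 92 as an interim, per-site, screened or evaluable count. It cannot be a screened count, because fewer people cannot be screened than are randomised. It is not the evaluable count either, because the Sample size section gives that as 82.

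The Recruitment section names the centres, dates and channels, so it is where site staff would look for the target. A site that worked to it would stop 18 participants before the number the power statement relies on. With two totals in the text, any final count from 92 to 110 could be called on plan. A later reader could not tell whether the trial met its target, or whether the stopping point was chosen in the light of the data.

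**Working it through.** **Inputs, all from the Sample size section unless noted.** Two-group by two-time-point repeated-measures ANOVA, α = 0.05, target power 0.90, correlation between measures ρ = 0.4, effect size f = 0.2, required N = 82 (41 per arm), dropout allowance 25%, recruited N = 110 (55 per arm). Competing recruited N = 92 (Recruitment section).

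**Step 1: reproduce 82.** For the within-between interaction, G*Power uses a noncentral F with λ = f² × N × m / (1 − ρ), m = 2 time points, and 1 and N − 2 degrees of freedom.

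- N = 80: λ = 0.04 × 80 × 2 / 0.6 = 10.67, power 0.897.
- N = 82: λ = 0.04 × 82 × 2 / 0.6 = 10.93, power 0.904.

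So 82 is the smallest even total that reaches 0.90, as the plan states.

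**Step 2: reproduce 110.** 41 / (1 − 0.25) = 54.7, rounded up to 55 per arm, 110 in total. This treats 25% as the fraction lost. Adding a quarter to 82 instead gives 82 × 1.25 = 102.5, which is not 110.

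**Step 3: try to derive 92.** Neither reading gives it: 82/0.75 = 109.3 and 82 × 1.25 = 102.5. The loss at which 92 recruits leave exactly 82 is 1 − 82/92 = 10.9%. A 10% loss would call for 82/0.9 = 91.1, so 92 would suit a dropout assumption of 10 to 11%, but the article states no such assumption.

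**Step 4: what 92 delivers, with the plan's f and ρ.**

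| Recruited | Loss | Completers | Power |
|---|---|---|---|
| 110 | 25% | 82.5 (82 needed) | 0.904 at 82 |
| 92 | 25% | 92 × 0.75 = 69 | 0.848 |
| 92 | 20% | 92 × 0.80 = 73.6 | about 0.87 |
| 92 | 10.9% | 82 | 0.904 |
| 92 | none | 92 | 0.934 |

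The 20% row is the loss implied if the allowance means adding a quarter to the requirement, since 1 − 1/1.25 = 0.20. The shortfall against 82 is 13 completers at 25% loss and 8 to 9 at 20%.

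**Side calculation.** If d = 0.4 is a post-treatment difference with equal baselines, the four interaction effects are ±0.1 SD, so f = 0.1 rather than 0.2. Power is then 0.372 at N = 82 and 0.321 at N = 69. That conversion is a separate question about the Sample size section, and the conflict between 92 and 110 does not depend on it.

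**The case against.** The strongest reply is that 92 is a leftover in a parenthesis. The only derivation in the article leads to 110 and the Abstract agrees, so a careful reader can tell which number is meant. Recruitment is also bounded by calendar dates, and nothing says that sites close on the count in the Recruitment section. No interim look at outcomes is described, and the statistician is blinded. These points stand as far as they go. A derived target does exist, early closure is a conditional risk, and any suggestion of a data-driven stop concerns appearance only.

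A second point is that 69 rests on reading the allowance as a 25% loss, which is not its literal wording. That is correct, but it is the reading that reproduces 110, and the shortfall survives the other one.

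A third is that the effect is modest, and that completers are not the analysis set: all randomised participants enter the intention-to-treat analysis, with multiple imputation planned for the primary outcome. The effect is indeed moderate. Imputation does not restore all the lost information, however, and the plan's own inflation for dropout treats 82 as the number that must remain.

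Finally, the arithmetic in the Sample size section is sound, so this is an inconsistency between sections rather than a miscalculation. None of these points explains 92.

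**Conclusion.** The concern holds. The enrolment figure in the Recruitment section contradicts both the Abstract and the only derivation in the article, and no stated assumption produces it. If 92 were used, the trial would end with about 69 to 73 completers against the 82 required. Power on the plan's own inputs would be about 85 to 87% instead of 90%. This rests on the stated f = 0.2 and ρ = 0.4 and on losses of 20 to 25%. With loss at or below 10.9% there is no shortfall, and with no loss power would be 93%. The power cost is therefore moderate. The main reason to correct it is that a planned sample size must be a single number. The article does not show which figure the sites or the registry use.

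**What to change.** In the Recruitment section, replace 92 with 110 (55 per arm), matching the Abstract and the Sample size section. Confirm that site documents and the registry entry carry the same target. If the sponsor did intend 92, it should instead state the dropout assumption behind it (at most 10.9% to retain 82) and revise the other two places to match.

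The default correction changes one number and requires no enrolment beyond what the plan already states.

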### Procedure

#### Screening

The study is open for both clients who are already a patient in one of the participating centers and new patients. Both new, chronic, and recurrent PTSD patients are included, and for all participants, the inclusion criterion is a current DSM-5 diagnosis of PTSD. The candidate participant will be invited to the clinic and asked for oral and written informed consent. Next, the participant will be administered the SCID-5 by a trained assessor. The following self-report questionnaires will also be administrated: sociodemographic questions (i.e. gender, age, ethnic), medical history (i.e. medical intervention, kind of drug consumed), and the PCL-5 (PTSD Checklist for DSM-5) [26]. If a candidate meets the inclusion criteria and none of the exclusion criteria, the participant will be invited to the next step of the baseline assessment after a break of 15 min.

A research assistant will provide information about the purpose of the study, including the background rationale of the study, risks and safety, benefits, and their right to withdraw from the study at any time without consequences. The participants will be asked oral and written informed consent for the RCT before entering the study.

The research assistant will continue the baseline assessment by administering the Hopkins Symptoms Checklist-25 (HSCL-25) [27], the Perceived Stress Scale (PSS [28];), and the World Health Organization Quality of Life (WHOQOL-BREF [29];). Neurocognitive tests administered at baseline include the Trail Making Test (TMT) [30], California Learning Verbal Test (CLVT [31];), and Subtest Digit Span of the Wechsler Adult Intelligence Scale fourth edition (WAIS-IV) [32]. Finally, participants will be instructed on how to collect saliva for cortisol analyses.

The second part of the baseline assessment includes the physiological measurements, using the VU University Ambulatory Monitoring System (VU-AMS) device when the participant listens to the traumatic script. The physiological measurements are performed 1 week after the T0, directly before the first treatment session. The reason is that the traumatic script needed for the physiological measurements will be prepared based on the information gathered at the T0. The recording procedure of VU-AMS is explained in the stress measurement section.

#### Randomization

After all baseline assessments have been completed, randomization will be conducted. We use the randomization tool that is included in the Castor data management software (www.castoredc.com). Participants will be allocated in a 1:1 using block randomization into one of two conditions: (1) EMD and (2) retrieval-only control which consists of the EMD protocol without the EMs. Block sizes of 4, 6, and 6 will be selected randomly within the randomization process. The time span between T0 and the first intervention session will be approximately 1 week.

At post-treatment after the final session, the PCL-5, HSCL-25, PSS, WHOQOL-BREF, TMT, CVLT, Digit Span, HRV/HR, PEP, and saliva collection for cortisol will re-administered. Then, 1 month (T2) and 3 months (T3) after the final session, the PCL-5, HSCL-25, PSS, WHOQOL-BREF, TMT, CVLT, and digit span WAIS-IV subtest will re-administered. The follow-up assessment will be performed in two steps. First, participants will be contacted personally and motivated to complete the follow-up assessment. In case participants refuse, they will be offered an assessment of primary outcome only. If participants still refuse, they will be asked to provide reasons for their refusal, which will be documented.

#### Blinding

The study is single blind. Participants will be informed about the condition they are assigned to. The research coordinator and therapist will not be blinded to treatment allocation. The assessors are blinded, meaning that an assessor is not aware of the condition to which the participant is assigned. The statistical analysis will be performed by statistician who is blinded to treatment allocation. The statistician is a doctoral researcher who is an expert in data analysis using R statistics software.

#### Stress measurement

Physiological responses to scripts (see script-driven imagery [33];) are acquired by using the VU-AMS device, which records the electrocardiogram (ECG) and the impedance cardiogram (ICG) continuously through seven disposable electrodes. The reliability and validity of the VU-AMS device have been reported as adequate [34]. Stress reactivity will be measured through HR/HRV and PEP variables. HRV and pre-ejection period show variability and are indicators of cardiac autonomic nervous system activity (sympathetic drive by pre-ejection period, and parasympathetic drive by HRV) [35].

The recording process will be held in a private area or any location that is relatively quiet and free of noise. The participants will be seated in a comfortable chair, and their feet should be able to reach the floor. The participants should not do the following activities at least 1 h prior to the recording: heavy aerobics, consumption coffee, tea, or other caffeine. No cigarettes should be smoked from 30 min before the recording. Participants are asked to wait at least 1½ h after a heavy meal to take the measurement. Current medications are recorded. Research staff will explain to participants that the goal of this session is to gather information about stress responses to trauma scripts. They also will be informed that excessive movement may result in artifacts and therefore, they are asked sit quietly without talking, falling asleep, crossing legs, or making unnecessary movements. It is preferable that participants keep their eyes open. The test leader will place 7 electrodes on the surface of the participant’s skin. After attaching the electrodes, the test leader checks the signal on the monitor screen. If the signal looks stable, then the recording process is ready to begin (see Fig. 2, lead electrodes placement).

**Fig. 2 Fig2:**
[figure not shown]
Lead electrodes placement

#### Script-driven imagery

Stress responses to neutral and traumatic stimuli will be measured using the script-driven imagery procedure [33]. For the current study, the researcher prepared “visiting the national library” as a neutral script. Personalized traumatic scripts will be made based on of participants’ trauma narratives. The participants are first asked to describe their traumatic event in detail, which the interviewer will write down in about 450–500 words. The story includes a mental image of the traumatic experience that produces distress. This traumatic script will be read and audio-recorded by an independent female person. The recordings of the neutral and trauma scripts will be played during physiological stress assessment using the VU-AMS device [36].

